### Data analysis

Participants who have completed 80% of the prescribed treatment will be considered for per protocol (PP) analysis and all the patients who were randomized will be taken for intention-to-treat analysis. Modified intent-to-treat (mITT) will be performed after excluding: (a) patients with DR TBM detected after randomization; (b) diagnosed to have any other meningitis such as bacterial, viral, and fungal after randomization; (c) patients refused to be part of the trial when the initial consent was obtained from legally authorized representative; and (d) receiving less than 2 months of administration of the randomized study drugs for reasons other than death.

An interim analysis is planned at two time points during the study period, viz. after 33% and 66% of the enrolled patients have completed 8-week treatment. In addition, the interim analysis may be done if the frequency of reported serious adverse events is greater than anticipated. Reports will be provided to the DSMB at these time points.

Baseline variables will be summarized between the groups using appropriate summary statistics based on the level of measurement. The time to composite outcome will be estimated using Kaplan–Meier survival estimate and it will be compared between the three arms using Log rank test. The factors associated with time to death or disability will be assessed using Cox proportional hazards regression analysis. This is a superiority trial and we will perform two-sided tests and use type I error alpha value of 5% to claim superiority between two groups.

The analysis for the primary outcome will be stratified based on HIV status and baseline severity of the disease measured by MRC. Sensitivity analysis will also be done including only definite and probable cases of TBM. The Cox proportional regression will be summarized using hazard ratio and 95% confidence interval. Extended Cox regression will be used in lieu of proportion Cox regression if the proportional hazard assumption is violated. The AE data will be summarized using frequency and percentage and compared between the regimens using Chi-square test. In addition, count regression models will be used to compare the number of AEs between the regimens after adjusting for other variables. Maximum plasma concentration (*C*max), time for maximal concentration (*T*max), and area under the curve (AUC) will be measured and correlated with treatment outcomes and occurrence of adverse events using log binomial regression model. Influence of PK parameters on treatment outcome will be identified using multivariable regression analysis. The quality of life will be summarized using mean and standard deviation. The variable will be compared between the regimens using ANOVA or the non-parametric alternative, Kruskal–Wallis test.

We will deal the missing data using multiple imputation technique depending on the missing data mechanism.

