### Treatment allocation

#### Arm 1 (intensified ATT with aspirin)

Participants in this arm will receive a high dose of rifampicin 25 mg/kg once daily and moxifloxacin (400 mg once daily) along with isoniazid and pyrazinamide for 2 months. Steroids will be administered to participants with MRC grades 1 and 2 for a duration of 6 weeks, while participants in grade 3 will be treated for 8 weeks. This regimen will also be intensified with 150 mg of aspirin once daily. Intensive phase will be followed by standard doses of rifampicin, isoniazid, and pyrazinamide for the next 4 months in the continuation phase (Fig. 1).

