#### Arm 3 (control arm)

The control arm will receive treatment according to the standard national guidelines for TBM. They will receive a first-line regimen consisting of 2 months of isoniazid, rifampicin, ethambutol, and pyrazinamide followed by 10 months of isoniazid, rifampicin, and ethambutol daily in a fixed-dose combination (FDC) as per the various weight bands in National TB Elimination Programme of India. Participants will also receive steroids as in the other two arms.

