### Patient compliance

The drugs will be administered under supervision (except on Sundays) to ensure compliance. The importance of adherence to the treatment schedule will be reinforced at each visit. The cause for non-adherence will be identified. If the patient misses drug doses in the intensive phase (IP), it will be compensated at the end of the intensive phase. The compensation will be given for a maximum period of 15 days to complete 60 doses of the assigned regimen in the IP. Similarly, the missed doses in the continuation phase (CP) will be compensated at the end of CP so as to complete 120 doses in CP. Patients who do not attend treatment continuously for more than a month will be considered as lost to follow-up. For these patients, a minimum of two rounds of three attempts to contact them (telephonic/home visit) will be made. If these attempts are unsuccessful, then the participant will be considered lost to follow-up.

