### Criteria for discontinuing interventions

*Grade 2 toxicities:* For grade 2 toxicities, the patient will be followed more carefully, with additional laboratory and/or clinic visits as necessary, and the study drugs temporarily held at the investigator's discretion.

*Grade 3 toxicities:* For any grade 3 toxicity that in the investigator’s judgment is due to study drug(s), the causative study drug(s) will be held. The clinician will rule out other possible causes of the symptoms before discontinuing study medication. When possible, concomitant medications will be held first at the discretion of the investigator if he/she suspects they are contributing to the toxicity. Depending on the nature and severity of the toxicity, the degree to which it resolves, and/or the emergence of alternative explanations for the toxicity or the participant’s deterioration, the study drugs(s) may be restarted at the discretion of the investigator.

*Grade 4 toxicities:* Study drug will be permanently discontinued in any participant with grade 4 renal, hepatic, cardiac, or hematological toxicity.

For all toxicities that are treatment-emergent and require the study therapy to be temporarily or permanently discontinued, relevant clinical and laboratory tests will be obtained as clinically indicated and repeated as needed until final resolution or stabilization of the toxicity.

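### The per-protocol rule does not exempt deaths, and its 80% point falls at about 4.8 months in the intensified arms but 9.6 months in control, biasing that comparison against the intensified regimen

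*Protocol article*

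**What the plan says.** The Data analysis section defines three analysis sets.

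- Intention-to-treat: "all the patients who were randomized will be taken for intention-to-treat analysis".
- Per-protocol: "Participants who have completed 80% of the prescribed treatment will be considered for per protocol (PP) analysis". Nothing is said about patients who die before reaching 80%.
- Modified intention-to-treat, with four exclusions. The fourth, rule (d), is "receiving less than 2 months of administration of the randomized study drugs for reasons other than death".

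The regimens differ in length. In arm 1, after a 2-month intensive phase, "Intensive phase will be followed by standard doses of rifampicin, isoniazid, and pyrazinamide for the next 4 months in the continuation phase". Arm 2 follows the same timetable. Control has 2 months of four drugs "followed by 10 months of isoniazid, rifampicin, and ethambutol daily in a fixed-dose combination (FDC"). That is 6 months against 12.

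Patient compliance gives one dose target, without separating the arms: "the missed doses in the continuation phase (CP) will be compensated at the end of CP so as to complete 120 doses in CP". The intensive-phase target is 60 doses.

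Under Outcome measures, the primary outcome is time from randomisation to death or disability, and all-cause mortality is an outcome in its own right.

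**The concern.** Membership of the per-protocol set should depend on adherence. As written, it also depends on staying alive. A patient who takes every dose and dies at month 3 has not completed 80% of treatment in any arm and is removed. A patient who takes every dose and dies at month 7 is an event in arms 1 and 2, where the 80% point has passed, but is deleted from control, where it has not. The rule therefore selects on the primary event, and more severely in control.

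At stake is whether the per-protocol result can be set beside the intention-to-treat result. If control loses deaths that the intensified arms keep, the two analyses can disagree for a reason unrelated to treatment, and a real benefit could look as if it fades among patients who took their drugs.

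**Working it through.** **Inputs from the protocol article.** Sample size: 24% mortality and 32% disability, so 24 + 32 = 56% composite, as stated there; 124 patients per arm. The stated 112 per arm before losses is close to the 110 given by a pooled two-sided z test at 85% power, and is not in question. Treatment length is 6 months (arms 1 and 2) and 12 months (control). The article gives no figure for the per-protocol set and no timing of deaths.

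**Cut-offs.** 0.80 × 6 = 4.8 months; 0.80 × 12 = 9.6 months.

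**No true difference.** Give every arm 24% mortality by month 12 with Weibull death times (an assumption). Then S(12) = 0.76 and S(t) = 0.76^((t/12)^k), so S(4.8) = 0.76^(0.4^k) and S(9.6) = 0.76^(0.8^k). Let c be the arm's cut-off.

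- Share of 12-month deaths removed = (1 − S(c)) / 0.24
- Per-protocol 12-month mortality = 1 − 0.76 / S(c)
- Per-protocol composite = 1 − 0.44 / S(c), where 0.44 = 1 − 0.56 is the event-free share, none of whom are removed

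| | k = 0.4, arms 1–2 | k = 0.4, control | k = 1, arms 1–2 | k = 1, control |
|---|---|---|---|---|
| S(c) | 0.8268 | 0.7780 | 0.8960 | 0.8029 |
| Deaths removed | 72% | 93% | 43% | 82% |
| Per-protocol mortality | 8.1% | 2.3% | 15.2% | 5.3% |
| Per-protocol composite | 46.8% | 43.4% | 50.9% | 45.2% |

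The false composite gap is 46.8 − 43.4 = 3.4 points (k = 0.4) and 50.9 − 45.2 = 5.7 points (k = 1), both against the intensified regimen.

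**Other death timings.** If s is the share of deaths before the arm's cut-off, the composite is 1 − 0.44 / (1 − 0.24s).

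| Assumed s, arms 1–2 / control | Composite, arms 1–2 / control | Gap (points) |
|---|---|---|
| 0.90 / 0.97 | 43.9% / 42.6% | 1.2 |
| 0.80 / 0.95 | 45.5% / 43.0% | 2.5 |
| 0.60 / 0.90 | 48.6% / 43.9% | 4.7 |
| 0.48 / 0.96 (even over 10 months) | 50.3% / 42.8% | 7.4 |

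**Error rate.** In a simulation of arm 1 against control (124 per arm, no true effect, 4,000 runs, two-sided 5% z test of proportions rather than the planned log-rank test), intention-to-treat rejected in 4.6% of runs. Per-protocol rejected in 5.8% to 9.9% from deaths alone (death-time scale 2 to 5 months). If disabled patients are also assumed to default three times as often (base rate 2% to 3% a month), this rises to 12% to 26%.

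**The control denominator.** Sixty doses over 2 months is 30 a month, and 120 over 4 months matches that rate. Ten months at the same rate would be 300. If the 120 applied to control, 80% of 60 + 120 = 180 doses is 144 doses, or 4.8 months, and the cut-offs would coincide. That does not fit the 10-month phase described for control, and adherent early deaths would still be removed.

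**Rule (d) of the modified set.** With 56% true risk in both arms, a fraction e removed and event risk r in those removed, the remaining risk is (0.56 − e·r) / (1 − e). No value of e or r is in the document. Take e = 10% to 20% in the intensified arm and 5% in control:

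- r = 0.70, e = 10%: 54.4% v 55.3%, 0.8 points for the intensified arm.
- r = 0.90, e = 20%: 47.5% v 54.2%, 6.7 points for the intensified arm.
- r = 0.50: 56.7% to 57.5% v 56.3%, 0.4 to 1.2 points against it.

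If early stopping is equal in both arms, simulation shows no gap.

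**The case against.** The strongest reply is that the main analysis is not at risk. The set of all randomised patients is defined in the same sentence as the per-protocol set and is unaffected. In a superiority trial, the bias from deaths also runs against the new regimen, so it cannot by itself produce a false claim of superiority. Both points stand, and they lower the severity. They do not make the per-protocol comparison interpretable.

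Several stronger readings are tempting but not supported.

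- A reader might carry the roughly threefold mortality excess over to the primary outcome. It applies to mortality alone. On the composite the ratio is about 1.1.
- A reader might infer that rule (d) shares the defect. It does not: it keeps early deaths, and its 2-month cut-off is the same in every arm. It does remove non-fatal stopping, including for toxicity; under Criteria for discontinuing interventions, "Study drug will be permanently discontinued in any participant with grade 4 renal, hepatic, cardiac, or hematological toxicity". But a bias favouring the intensified arms needs unequal stopping and above-average risk in those removed, and the sign reverses if their risk is below average. The Discussion, citing studies of high-dose rifampicin rather than of this full regimen, reports no increase in severe adverse events.
- A reader might suspect the exclusion of "patients with DR TBM detected after randomization", or of other meningitis found later, of picking out failing patients. Diagnostic CSF is scheduled only at pre-screening, so late results on specimens taken before randomisation are an adequate explanation.
- A reader might object that no set is named as primary. That can be left to the statistical analysis plan.

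**Conclusion.** The point holds for the per-protocol set and is of moderate weight. Applied as written, the rule removes adherent patients because they died, up to about 4.8 months in arms 1 and 2 and 9.6 months in control. With equal 24% mortality, the false gap on the composite is 3 to 6 points under Weibull death times of shape 0.4 to 1.0, and 1 to 7 points across the other timings tried, always against the intensified regimen. The 6- and 12-month durations and the lack of a death exemption come from the document; the timing of deaths is assumed, and the gap shrinks if nearly all deaths are early. The 12% to 26% rejection rates rest on a further assumption about default and should not be quoted as the effect of the rule alone.

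The modified intention-to-treat set is a secondary matter. It can be biased in either direction if early stopping differs by arm and relates to prognosis, so it should be read only in support of intention-to-treat.

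**What to change.** 1. Define the per-protocol set as patients who took at least 80% of the doses due from randomisation to the earlier of death and end of assigned treatment. Adherent patients who die then stay in as events, in line with the exemption for death that rule (d) already makes. Under no true effect, and before any default, the composite returns to 56% in both arms.
2. Reconcile the 120 continuation-phase doses under Patient compliance with the 10-month phase under Arm 3, so that control's denominator is defined.
3. State that the per-protocol and modified intention-to-treat results support the intention-to-treat result and do not stand in for it.

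The cost is a few lines of wording and a doses-due calculation; dosing is supervised except on Sundays, so the records should exist. The downside is a larger per-protocol set that is less strictly treatment-complete. The change does not remove selection through default, since control patients still have twice as long in which to fall below 80%. That is a further reason for item 3.

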**Discussion:**

Current WHO regimens have agents with poor central nervous system drug exposure and is too long. It does not reflect the accumulating evidence in the field. We propose a comprehensive clinical trial incorporating the emerging evidence accrued over the last two decades to shorten the duration and improve the treatment outcomes. This multi-centric trial may generate crucial evidence with policy and practice implications in the treatment of TBM.

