In designing this trial, our approach is guided by two principles. We wanted the intervention to reflect the improvements made in the field recently, including high-dose rifampicin and addition of fluoroquinolones and aspirin. We propose a novel clinical trial to demonstrate the efficacy of short course therapy compared to standard of care. The drugs and doses proposed in this trial have individually been shown to be beneficial and efficacious in the treatment of pulmonary tuberculosis and TB meningitis. However, they have not been evaluated for cumulative benefit. The INTENSE TBM trial that used high-dose rifampicin and linezolid evaluated mortality alone as an outcome and considered 30% reduction in mortality [14]. We hypothesize that intensified short course (6 months) ATT with high-dose rifampicin and moxifloxacin given along with corticosteroids and aspirin will significantly reduce mortality and disability in adults with TBM compared to 12 months of standard ATT regimen. We assume our study regimen will be superior to the control regimen in terms of reducing death or disability by at least 20%.

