### Participant timelines and follow-up

In this assessment, demographic details, medical history, clinical examination, neurological assessment including Modified Rankin Score (MRS) and Glasgow Coma Scale (GCS), sociological assessment for compliance to trial procedures, and all other study procedures will be done. Blood will be collected for hematological (complete blood count—CBC) and biochemical tests (sugar, HbA1C, liver, and renal function tests), HBsAg, and HIV. Patients will also undergo CT or MRI imaging of the brain. We will also collect sputum for CBNAAT and AFB culture and do chest X-ray to rule out pulmonary TB. All eligible patients will be enrolled into the trial. At the time of enrolment, blood will be collected for immunological biomarkers (CRP, TNF-α, monocyte and dendritic cell functions, and other cytokines).

During the study period, patients will be followed as per the study schedule attached (Table 1). After admission to the study and treatment allocation, participants will be followed up every week for the first 2 months and monthly till the completion of the treatment. They will undergo clinical examination including detailed neurological examination and adverse event (AE) monitoring. After treatment completion, all participants will be followed up once in 3 months for a period of 12 months. Participants in the study arms I and II will complete 12 months of post-treatment follow-up at the 18th month study visit and participants in the control arm will complete their post-treatment follow-up at the 24th month study visit.

**Table 1 Tab1:** Study schedule

S No	Investigations	Pre-screening	Screening	Enrolment	W1	W2	W3	W4	W5	W6	W7	W8	M3	M4	M5	M6	M7	M8	M9	M10	M11	M12	M15	M^a^18	M21	M24
1	Screening consent		✓																							
2	Assess eligibility		✓	✓																						
3	Informed consent			✓																						
4	History and clinical examination		✓	✓	✓	✓	✓	✓	✓	✓	✓	✓	✓	✓	✓	✓	✓	✓	✓	✓	✓	✓	✓	✓	✓	✓
5	GCS		✓	✓	✓	✓	✓	✓	✓	✓	✓	✓	✓	✓	✓	✓			✓			✓	✓	✓	✓	✓
6	Modified Rankin’s score		✓	✓	✓			✓				✓		✓		✓			✓			✓	✓	✓	✓	✓
7	Sputum smear and MGIT^b^		✓																			✓		✓		
8	CSF analysis for AFB smear, MGIT, Xpert, and to rule out other etiology as appropriate	✓																								
19	CSF cytology, biochemistry,	✓																								
10	HIV		✓																							
11	Urine pregnancy test^c^		✓					✓				✓	✓	✓	✓	✓	✓	✓	✓	✓	✓	✓				
12	Hepatitis B and C		✓																							
13	LFT		✓			✓		✓		✓		✓		✓		✓			✓			✓				

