### Outcome measures

Our primary outcome is mortality or disability which will be measured between inclusion and month 12 and month 24, i.e., time from randomization to death or disability during the follow-up period. All-cause mortality also will be considered as an outcome in the study. Survivors will be censored at the date they were last known to be alive (i.e., date of last follow-up visit, loss to follow-up or withdrawal). All-cause mortality rate will be measured in proportion and disability will be measured by modified Rankin scale. We will classify the score as “no disability” (a score of 0), “mild to moderate disability” (score of 1–2), and “severe disability” (3–5).

Grade 3 or 4 AEs will be measured in proportion according to Division of AIDS (DAIDS) criteria at the end of 12 months [18]. The DAIDS criterion categorizes adverse events as “mild events” (grade 1), “moderate events” (grade 2), “severe events” (grade 3), and “potentially life threatening events” (grade 4). Pharmacokinetic outcome measures will be plasma concentration time-curve during the dosing interval (AUC), peak plasma concentration (*C*_max_), and CSF concentration. Time to reach maximum plasma concentration (*T*_max_) of the study drugs will be measured up to week 8. Quality of life at baseline and 6 months, 12 months, and 24 months will be assessed in mean and standard deviation using a WHO Short form-36 (SF-36) questionnaire. It is a commonly used generic health-related quality of life (QoL) instrument which consists of 36 questions measuring health in different dimensions covering physical, mental, and social well-being of the patients. SF-36 was adapted and translated into several language and its validity and reliability were already established in India in TB context [22, 23].

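### mITT exclusions (a) and (b) are not limited to specimens taken before randomisation, so they also remove resistance and meningitis that arise afterwards

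*Protocol article*

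**What the plan says.** The Data analysis section of the protocol article defines three sets. For ITT, "all the patients who were randomized will be taken for intention-to-treat analysis". Per protocol requires 80% of the prescribed treatment. The mITT set drops four groups. Two of them concern this point: (a) "patients with DR TBM detected after randomization" and (b) those "diagnosed to have any other meningitis such as bacterial, viral, and fungal after randomization". Neither has a time window or refers to a baseline specimen or a condition present at entry. The section does not say which set supports the superiority claim.

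Under Study population and eligibility criteria, exclusions (1) and (2) already bar known drug resistance and any other known meningitis at entry. Under Outcome measures, the primary outcome is "time from randomization to death or disability during the follow-up period".

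**The concern.** A modified ITT set is defensible when it removes patients who were ineligible on facts fixed before randomisation, even if the laboratory result arrives later. That is presumably the purpose here, but the wording turns on when the finding is made and not on when the specimen was taken. A patient who worsens in month 9 and then yields a resistant isolate meets (a). A patient who develops a new bacterial meningitis during care meets (b).

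These are events after randomisation. They may depend on the assigned regimen and on how the patient is doing, so excluding on them breaks the comparison that randomisation protects. At stake is whether the mITT result can be read as a fair comparison of the regimens.

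**Working it through.** **The plan's own figure.** The exclusions do not enter the sample size, which reproduces closely. With 56% against 36%, two-sided 5% and 85% power, the pooled formula is n = [1.960 × √(2 × 0.46 × 0.54) + 1.036 × √(0.56 × 0.44 + 0.36 × 0.64)]² / 0.20², which gives 110 per arm against the stated 112. Then 112 × 1.1 = 123.2, rounded up to 124, and 3 × 124 = 372. There is no arithmetic fault.

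**The passages side by side.**

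- Entry exclusions (1) and (2) deal with resistance and other meningitis known at screening. What is left for a legitimate mITT exclusion is a baseline specimen whose result comes late.
- Exclusions (a) and (b) cover that case, and also any finding up to the end of follow-up (month 18 in arms 1 and 2, month 24 in control).
- In Table 1 (Study schedule), CSF microbiology and CSF cytology and biochemistry are ticked only at pre-screening. The one later planned CSF sample is for pharmacokinetics in a subset. A later CSF diagnosis therefore comes from unscheduled testing, and a patient who is doing badly is the likelier one to be tested.
- The trial is open label, and the Randomization section says that the site investigators are also the treating physicians. Those who decide on such a test know the arm.

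**Illustration of size.** The documents give no rate of late resistance or late meningitis, so the number removed, k, is an assumption. Arm 1 has 124 patients; at the planned 36% that is 124 × 0.36 = 44.64, or 45 events: 45/124 = 36.3%.

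If the removed patients all had the event, the rate is (45 − k)/(124 − k):

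- k = 2: 43/122 = 35.2%
- k = 4: 41/120 = 34.2%
- k = 6: 39/118 = 33.1%

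If none of them had the event, it is 45/(124 − k):

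- k = 2: 45/122 = 36.9%
- k = 4: 45/120 = 37.5%
- k = 6: 45/118 = 38.1%

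Six removals from one arm thus move its rate by at most 3.2 points down or 1.8 points up. Removals from control move the control rate by the same mechanism.

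**False positives in mITT under a one-sided assumption.** Suppose there is no true effect (56% in both arms, 112 per arm, so 62.72 expected events), and k patients with events are removed from one arm only. That arm's rate becomes (62.72 − k)/(112 − k). For k = 4 this is 58.72/108 = 54.4%, a spurious 1.6 points. For k = 8 it is 54.72/104 = 52.6%, a spurious 3.4 points. By the normal approximation to the two-sided two-proportion test, the rejection rate rises from 5% to 5.7% and 7.9%. This is a deliberately unfavourable case, not a forecast.

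**The case against.** The strongest reply is that (a) and (b) mirror the entry exclusions, and that the only scheduled CSF culture is taken before randomisation, so the natural reading is late results from baseline specimens. That is probably the intention. It does not settle the matter, because an analyst who follows the rule as written would also remove later findings.

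Second, ITT is planned on everyone randomised and nothing is deleted there; a deterioration that leads to death or qualifying disability is counted. This stands and limits the point to mITT. The SAP may name the primary set, but the article does not.

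A reader might infer three stronger things, and the documents do not support them.

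- That the exclusions make the 6-month regimen look better. They apply to all arms, no rates are given, and removing patients without events moves the rate against the arm that loses them.
- That Table 1 footnote b shows symptom-driven testing for meningitis. It marks only sputum and chest X-ray. The argument for selective testing rests on the absence of scheduled follow-up CSF.
- That the lack of a recurrence outcome is an error. The stated objective is superiority on death or disability, the modified Rankin score is scheduled through follow-up, and a condensed article may leave further outcomes to the full protocol. A recurrence with lasting functional effect can be captured by the primary outcome.

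Finally, (b) carries less weight than (a), since a new bacterial, viral or fungal meningitis is not in itself a failure of TB treatment.

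**Conclusion.** The point holds for the wording of the mITT exclusions. As stated, (a) and (b) remove patients on findings that can arise after randomisation and can depend on outcome and arm. The planned ITT analysis is unaffected.

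The direction of any bias is unknown. Its size is probably modest: with 2 to 6 removals from arm 1, the 36.3% rate would lie between 33.1% and 38.1%, against a planned 20-point difference. That range rests on the assumed number of removals, on all of them falling in one arm, and on the two extremes of all or none having had the event. The point matters most if the superiority claim were to rest on mITT, which the article leaves open.

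**What to change.** Reword (a) and (b) so that they apply only to drug resistance or another meningitis shown on a specimen collected before randomisation; the result may come later. Have these exclusions judged without knowledge of the arm where possible. Keep patients with later findings in mITT. State that the superiority claim rests on ITT and that mITT is supportive.

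The cost is a change of phrase in the mITT definition and one sentence naming the primary set. It needs no extra visits or tests, and mITT keeps a few more patients. The Trial status section says that recruitment had not begun, so the change could be made before any data exist.

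Optionally, and not as part of the error, recurrence or retreatment of TBM could be reported from the existing visits. If it is counted after treatment completion up to month 18, arms 1 and 2 have 18 − 6 = 12 months off treatment and control has 18 − 12 = 6, so the report would have to state this imbalance.
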